### Sample Size

Using data from a previous observational study evaluating one-year statin adherence of new users at 34 different community pharmacies in Saskatchewan [21], we were able to estimate an intracluster (or intraclass) correlation coefficient (ICC) of 0.0143, and determine that mean statin adherence in this population was 0.71 (SD 0.13). Thus, in order to detect a 15% improvement in mean adherence, considered to be clinically important [24,25], 270 subjects would be required in each group to detect a difference of approximately 15% with 80% power at a p < 0.05. The community pharmacies enrolled in CPATCH are expected to accrue a minimum of 25 subjects over a 6 month period. As a result, 22 clusters (pharmacies) are calculated as needed, but 30 will actually be enrolled as the planned statistical analysis requires a minimum of 15 clusters within each group [26].

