We describe the design of a study aimed at evaluating the real-world effectiveness of an adherence intervention provided by community pharmacies; the Community Pharmacy Assisting in Total Cardiovascular Health (CPATCH) study. This prospective study employs a novel design that integrates cluster randomization with an evaluation of *all *at-risk patients using an administrative database. This design presented herein was developed to strengthen the external validity of research studies that examine adherence interventions while maintaining the high standards required for prospective clinical trials. Although the general CPATCH strategy is intended to be employable with all cardiovascular medications, this study is focused on the prevention of non-adherence among new users of statin medications. Statin medications were chosen for this initial study, as it is well known that 40% to 50% of all new statin users become non-adherent within the first year [12,13], and a sizeable proportion discontinue the medication after only one dispensation [14].

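### The 270 subjects per group for 80% power does not follow from the mean, SD, ICC and 15% difference printed beside it

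*Protocol article*

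**What the plan says.** The planning values in the Sample Size section come from an earlier observational study of new statin users at 34 Saskatchewan pharmacies. That study gave an "intracluster (or intraclass) correlation coefficient (ICC) of 0.0143" and showed that "mean statin adherence in this population was 0.71 (SD 0.13" (closing bracket omitted here). The aim is "in order to detect a 15% improvement in mean adherence". The section then draws its conclusion directly from these values: "270 subjects would be required in each group to detect a difference of approximately 15% with 80% power at a p < 0.05".

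Each pharmacy is expected to contribute at least 25 subjects in six months, from which the section calculates 22 pharmacies. It enrols 30 for a separate reason: the planned analysis is said to need at least 15 clusters per group.

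The section does not say whether 15% is relative or absolute, whether the test is one- or two-sided, or what design effect was used. The Outcomes section makes the primary outcome a mean of individual proportions of days covered (PDC), so the matching calculation is a comparison of two means.

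**The concern.** Against an SD of 0.13, a difference of 0.11 to 0.15 is about one standard deviation. Detecting a shift that large takes a few dozen subjects per group, and an ICC of 0.0143 with 25 per cluster adds only about a third. A requirement of 270 is out of scale with these inputs.

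The inputs and the result stand in the same paragraph, one offered as the consequence of the other, so the mismatch cannot be put down to detail left out of a condensed article. At stake is whether the planning statement can be relied on. As printed, a reader cannot tell whether the trial was sized to detect a difference near 0.03 or near 0.09.

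**Working it through.** **Inputs (Sample Size section).** Mean 0.71; SD 0.13; ICC 0.0143; 25 subjects per pharmacy; power 80%; alpha 0.05. Assumption: two-sided test, so (1.960 + 0.842)² = 7.849. Difference d = 0.15 × 0.71 = 0.1065 if relative, 0.15 if absolute.

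**The step that reproduces.** 2 × 270 = 540; 540 / 25 = 21.6, rounded up to 22 pharmacies. The break lies before this step.

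**Design effect.** 1 + (25 − 1) × 0.0143 = 1.3432.

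**Required size from the printed inputs.** n per group = 2 × 7.849 × SD² / d² × design effect.
- Relative: 2 × 7.849 × 0.0169 / 0.01134 = 23.4; × 1.3432 = 31.4, so about 32.
- Absolute: 2 × 7.849 × 0.0169 / 0.0225 = 11.8; × 1.3432 = 15.8, so about 16.

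The printed 270 is about 8 times (270 / 32) or 17 times (270 / 16) as large. Trying one- and two-sided tests at 80% and 90% power, with the design effect, gives 14 to 43 per group.

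**What 270 delivers at SD 0.13.** Standard error = 0.13 × √(2 × 1.3432 / 270) = 0.0130. Detectable difference at 80% power = 2.802 × 0.0130 = 0.036, about 5% of 0.71. For d = 0.1065, 0.1065 / 0.0130 − 1.96 is above 6, so power exceeds 99.9%; it is higher still for 0.15.

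**What would be needed to reach 270.**
- By the SD: 270 / 1.3432 = 201; SD = d × √(201 / (2 × 7.849)) = 0.38 (relative) or 0.54 (absolute).
- By the ICC, keeping SD 0.13: about 0.44 (relative) or 0.91 (absolute).
- By a different formula: treating 0.71 and 0.8165 as proportions, two-sided with continuity correction, gives about 268. This uses neither the SD nor the clustering; with the design effect it becomes 268 × 1.3432 = 360.

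None of these uses the stated mean, SD, ICC, difference and power together.

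**The trial as enrolled.** 15 × 25 = 375 per group. √(2 × 1.3432 / 375) = 0.0846.

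| SD | Standard error | Detectable difference (80%) | Power for 0.1065 |
|---|---|---|---|
| 0.13 | 0.0110 | 0.031 | > 99.9% |
| 0.38 | 0.0322 | 0.090 | about 91% |

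These use the normal approximation. A cluster-level t test on 30 pharmacies lowers the 91% to about 89%.

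**The case against.** The strongest defence is that nothing in the conduct of the trial depends on the 270. Thirty pharmacies are enrolled because of the analysis method, 25 subjects per pharmacy is a minimum, and new users are captured throughout each pharmacy's observation period. If SD 0.13 is right, the error is on the safe side. A null result would in any case be read from the GEE estimate and its interval, whose width depends on the observed variance. All of this stands, and it limits the consequence. It does not make the printed statement correct.

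Three stronger readings are tempting, but the document does not support them.
- *The SD of 0.13 must be the faulty input.* A reader might infer this from the Introduction, which says 40% to 50% of new users become non-adherent within a year and that "a sizeable proportion discontinue the medication after only one dispensation". Those statements rest on other cited studies. Turning them into an SD needs a stopping share, a fill length and a distribution that the article does not give. The calculation with proportions shows that a wrong formula could equally explain the 270.
- *An SD of 0.54 is impossible, so 15% must be relative.* The ceiling of √(0.71 × 0.29) = 0.454 holds only for a variable confined to 0–1. The Outcomes section defines PDC as total days' supply over days observed and states no cap.
- *All the planning values are passed on for reuse.* The Discussion offers only the ICC to other researchers, and nothing here shows the ICC to be wrong.

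**Conclusion.** The stated sample size and power are wrong on their own inputs. The printed values call for about 16 to 32 subjects per group where the article says 270, and 270 per group would detect about 0.036, not 15%. This rests on a two-sided 5% test, 25 subjects per pharmacy and the normal approximation; no choice of sidedness, nor 90% power in place of 80%, closes the gap. Which element is at fault cannot be settled from the article.

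A reader might infer that the trial is underpowered. The figures do not support that. At 375 per group, power for 0.1065 stays at or above 80% up to an SD of 0.1065 / (2.802 × 0.0846) = 0.449. The point is a reporting error that needs correcting. It leaves the design intact.

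**What to change.** Go back to the 34-pharmacy data and the original calculation, and reconcile four things without presuming which is wrong:
- the SD, confirming that 0.13 is the subject-level SD of one-year PDC;
- the difference, stated as relative or absolute with the target mean;
- the sidedness of the test;
- the formula, which should be for means with the design effect shown.

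Then restate the required number per group, and give the power or minimum detectable difference for the 30 pharmacies. At the 25-subject minimum, the latter is about 0.031 at SD 0.13 and about 0.090 at SD 0.38.

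The cost is one recalculation from the earlier study's data and a corrected paragraph. No further enrolment is needed.

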### Statistical Methods

Baseline characteristics will be compared between groups using both cluster and individual-level variables (Table 2). To determine the effect of the intervention, mean adherence will be measured at one year using generalized estimating equations (GEE) with an exchangeable correlation matrix and robust standard errors, with individuals as the analytical unit [27]. Both univariate and multivariable models will be developed based on individual and pharmacy-level variables considered statistically significant (P < 0.10), or clinically important (e.g. age, sex) (Table 2). All first order interactions will be tested.

**Table 2 T2:** Individual and Pharmacy Level Variables Available for Multivariable Analysis

Variable	Description	Database Source

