### Subjects

Intervention pharmacies will identify patients within the first year of statin therapy through dispensation records and face-to-face encounters. Although intervention pharmacies will target all statin users within their first year of therapy, data will only be collected on those subjects who: i) receive a new statin prescription from a study pharmacy (intervention or control) during the observation period; ii) have no statin fills recorded during the year prior to the index prescription (first fill for a statin medication during the study observation period); and iii) have been continuously enrolled as a Saskatchewan Drug Plan beneficiary for at least 365 days prior to the index prescription. These study subjects will be identified independently by personnel from the Saskatchewan Ministry of Health and all outcome data will be collected at the administrative database level (see "Follow-up").

The observation period for each pharmacy will begin two weeks after their training session. This two week lag period will be used to allow each staff to implement the strategy and resolve any issues with the help of the CPATCH investigators. To ensure consistency between groups, usual care pharmacies were assigned a start date that matched the date of an intervention pharmacy falling most closely in the order of randomization. As a result, in each permuted block of six randomized pharmacies, three pairs (one control and one intervention) of stores will share the same start date.

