The researchers will provide Sask Health with the list of participating pharmacies and their specific Saskatchewan Drug Plan identifiers (i.e., provider identifier), and enrolment dates. Sask Health personnel will extract all statin prescriptions dispensed from the participating pharmacies during the 18 months following the pharmacy's enrolment date. The individuals receiving these prescriptions will form the pool of potential new statin-users. The prescription histories of the potential pool members will be reviewed to determine which subjects are new statin-users. Hospital, physician and prescription information for eligible new statin-users will be compiled and de-identified prior to release to the researchers for analysis.

It is estimated that each pharmacy will need six months to accrue their sample size of new statin users, thereby allowing 12 months for follow up. However, because it will not be possible to determine when each pharmacy's sample size has been met, data will be collected on all new-users presenting to each pharmacy throughout the observation period. Subjects will be followed from one year prior to their index prescription until the end of the pharmacy's observation period, death, or loss of beneficiary status, whichever is sooner.

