### Outcomes

Although community pharmacies are the unit of randomization, our primary outcome is the mean statin adherence among all eligible new users of statin medications who have been followed up for at least 6 months past their index prescription. This primary outcome will be measured at the individual level. All statin dispensations for each subject will be captured by the prescription drug plan database and mean adherence will be measured using the proportion of days covered (PDC) [19,20], adjusted for any days that a subject may be hospitalized during the observation period. The PDC is calculated by taking the sum of the days' supply for all statin prescription fills during the study period, divided by the number of days of observation. Study participants who have statin dispensations from non-study pharmacies will be captured and accounted for using methods previously published [21]. Secondary outcomes include the proportion of new statin users who exhibit adherence (PDC) ≥80%, and the persistence with statin use among patients with a minimum of 12 months of follow up. Persistence is defined as the number of days from the index prescription to the earliest occurrence of study end date or date of discontinuation (assumed when a refill is not obtained within 102 days of finishing the estimated supply) [22,23]. Only those subjects with a minimum of 6 months of follow-up will be included in the secondary analyses.

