***Pharmacy Level***		

Pharmacy Type	Indicates the type of pharmacy (mass merchandise, chain/grocery, independent) [38]	Investigators to categorize

Pharmacy Location	Rural (population < 10,000)	Investigators to categorize
	Regional (population 10,000 - 100,000)	
	Urban (population > 100,000)	

Prescription Volume	Mean number of new statin prescriptions filled monthly (proxy measure for prescription volume)	Prescription Drug

Pharmacist Coverage	Pharmacist overlap or single pharmacist	Pharmacy survey

Technician Support	Pharmacy technician support	Pharmacy survey

Two secondary endpoints, the proportion of new statin users who exhibit optimal adherence (≥80%) at one-year and mean persistence will be measured on an individual level and analyzed using GEE with an exchangeable correlation matrix and robust standard errors. All analyses will be intention-to-treat, and will include any pharmacies that have withdrawn, as well as any individual subjects who are no longer beneficiaries of the Saskatchewan Drug Plan (due to death or coverage termination). Mean imputation will be used for subjects or pharmacies lost-to-follow-up.

Ethics approval for the study protocol was obtained from the University of Saskatchewan Biomedical Ethics Board (09-135). The study is registered at ClinicalTrials.gov no. NCT00971412.

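### Adherence is declared a one-year measure, but the population and denominator rules produce a mixture of 6- to 18-month values

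*Protocol article*

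**What the plan says.** Two sets of statements in the Protocol article define the adherence outcome.

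**One year.** Statistical Methods: "mean adherence will be measured at one year using generalized estimating equations (GEE"). After Table 2, the responder endpoint is "the proportion of new statin users who exhibit optimal adherence (≥80%) at one-year". Sample Size draws its mean (0.71), SD (0.13) and ICC (0.0143) from an observational study of one-year adherence.

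**Variable length.** Outcomes defines the primary outcome in all eligible new users "who have been followed up for at least 6 months past their index prescription", with days' supply "divided by the number of days of observation". It states no 365-day limit. Follow-up begins with a scheme that would give everyone a year: "each pharmacy will need six months to accrue their sample size of new statin users, thereby allowing 12 months for follow up". It then leaves accrual open: "data will be collected on all new-users presenting to each pharmacy throughout the observation period". Each subject is followed to the end of the pharmacy's observation period, death or loss of beneficiary status, whichever comes first.

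Two related inconsistencies sit beside this. Outcomes attaches a 12-month minimum follow-up to the secondary outcomes (at least to persistence) and then closes with a 6-month minimum for the secondary analyses. Follow-up dates the extraction "during the 18 months following the pharmacy's enrolment date", whereas Subjects says "The observation period for each pharmacy will begin two weeks after their training session".

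**The concern.** A subject with 6 to 12 months of observation cannot have a one-year PDC. A subject with 12 to 18 months does not get one either if the denominator is all days observed. Because new statin users stop over time, PDC falls as the window lengthens. A subject's score, and whether it clears 80%, would therefore depend partly on index date within the pharmacy's window.

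The stake is the definition of the primary outcome. Two analysts, one following Outcomes and the other Statistical Methods, would use different subjects and different denominators. The investigators are not blinded to allocation, so the choice should not be left until the data are in hand. The result would also not be the quantity for which the planning mean, SD and ICC were estimated.

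**Working it through.** **Inputs from the article.** 18-month window per pharmacy; follow-up to the end of that window; minimum 6 months for the primary outcome (Follow-up, Outcomes). At least 25 subjects per pharmacy in 6 months; 30 pharmacies, at least 15 per group; 270 subjects per group (Sample Size).

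**The plan's own figures.** The cluster count follows from the stated sample size: 2 × 270 / 25 = 21.6, so 22. The 270 itself is not reproduced from SD 0.13 with design effect 1 + 24 × 0.0143 = 1.343. A difference of 0.15 needs 12 × 1.343 = 16.1, so 17 per group; a difference of 0.1065 (15% of 0.71) needs 24 × 1.343 = 32.2, so 33. That is a separate matter. Here 270 serves only as the stated target.

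**Range of follow-up.** Potential follow-up = 18 − index month. Index at month 0 gives 18 months. The last admissible index, month 12, gives 6. This range needs no assumption about accrual.

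**Composition, with accrual constant at 25 per 6 months (assumed), 30 pharmacies.**

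| Index month | Follow-up | Per pharmacy | All 30 |
|---|---|---|---|
| 0–6 | 12–18 months | 25 | 750 |
| 6–12 | 6–12 months | 25 | 750 |
| 12–18 | under 6, excluded | 25 | 750 |

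Share of the admitted set below 12 months: 750 / 1,500 = 50%. If accrual in months 6–12 is k times that in months 0–6, the share is k / (1 + k): 33% at k = 0.5, 43% at 0.75, 56% at 1.25 and 60% at 1.5.

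**One patient.** Full coverage for 6 months, then stopping, gives 6/6 = 1.00, 6/12 = 0.50 or 6/18 = 0.33. The patient is a responder only if observed for no more than 6 / 0.8 = 7.5 months.

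**Group level (illustration).** Assume exponential discontinuation, full coverage until stopping, and a fraction S still on drug at 12 months, with S from 0.5 to 0.6. With h = −ln(S)/12, mean PDC over t months is (1 − exp(−ht)) / (ht), and the share at or above 80% is S^(0.8t/12).

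| Window | Mean PDC, S = 0.5 / 0.6 | PDC ≥80%, S = 0.5 / 0.6 |
|---|---|---|
| 6 months | 0.845 / 0.883 | 0.758 / 0.815 |
| 12 months | 0.721 / 0.783 | 0.574 / 0.665 |
| 18 months | 0.622 / 0.699 | 0.435 / 0.542 |

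**What the mixture does to the mean, S = 0.5.** With index dates even within each half-year, average PDC is 0.670 for follow-up of 12–18 months and 0.781 for 6–12 months.
- No cap, (0.670 + 0.781k) / (1 + k): 0.707, 0.725 and 0.736 at k = 0.5, 1 and 1.5, against 0.721 at one year.
- Cap at 12 months, (0.721 + 0.781k) / (1 + k): 0.741, 0.751 and 0.757.

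The mixed mean therefore differs from the one-year mean by −0.014 to +0.036, according to accrual and to which reading is used.

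**Whether a one-year restriction is affordable.** Subjects indexed in months 0–6: 15 × 25 = 375 per group, above 270.

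**The case against.** The best defence is that the randomised comparison survives. Subjects pairs an intervention and a control pharmacy on each start date, and every pharmacy has the same window length. Follow-up should be distributed similarly in the two arms, and the contrast is an average over those lengths. Under even accrual with no cap the mixed mean even lands near the one-year mean (0.725 against 0.721 above). This stands, and a reader should not infer between-arm bias. The near-agreement, however, depends on the assumed accrual pattern and on the uncapped reading, and it does not settle which subjects and denominator are primary.

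A second defence is that the one-year wording implies truncation at 365 days, a derivation detail that an article may leave out. That would narrow the range to 6–12 months, but it would give no one-year value to subjects with less than a year. The article prints both rules, so this is a conflict and not an omission. Mean imputation is reserved for losses to follow-up and is not offered for subjects whose follow-up is short by design.

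Two stronger readings fail. A reader might infer that half of the planned sample lacks a full year. The planned 25 per pharmacy fall in the first six months and all have 12 months of potential follow-up. The half concerns the larger set let in by open accrual, and only at a constant rate.

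A reader might also infer that extraction from the enrolment date brings in intervention patients who started before training. Subjects defines the index as the first fill within the observation period and excludes anyone with a statin fill in the preceding year; Follow-up treats the extraction only as a pool to be screened. The wording needs alignment, but that dilution does not follow.

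**Conclusion.** The conflict stands and nothing in the article resolves it. The 6-to-18-month denominator (6 to 12 with a cap) follows directly from the stated rules. The share of admitted subjects below 12 months is about 50% if the planned rate continues, and 33% to 60% over the accrual range shown.

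In the illustration the mean PDC differs by 0.18 to 0.22 between a 6-month and an 18-month window (0.883 − 0.699 and 0.845 − 0.622). Much of that cancels in a mixed average, but the cancellation is incidental. Those PDC figures rest on an assumed discontinuation curve and show direction and rough scale only.

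The consequence is an ill-defined estimand: a mean and a responder proportion that are not one-year values and do not match the planning inputs. The two definitions should be reconciled before outcome data are released.

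**What to change.** 1. Compute PDC and the 80% outcome over one fixed window: the first 365 days from index, in subjects whose index date is at least 365 days before the pharmacy's end date. Define eligibility by potential follow-up, and end the denominator at death or loss of coverage so that days after either are not counted as uncovered.
2. As a supporting analysis, report a fixed 180-day PDC in all subjects with at least 6 months of potential follow-up.
3. Align Follow-up, Outcomes and both parts of Statistical Methods with this, and settle the 12- versus 6-month minimum for the secondary outcomes.
4. Make the enrolment date in Follow-up the same date as the observation start in Subjects, and give that date to the Ministry.

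A fixed 6-month primary outcome would also remove the conflict. The 365-day window is preferable because it matches the planning inputs and the 6-plus-12-month scheme in Follow-up.

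The cost is derivation wording and one date definition, with no new data. The downside is that subjects accrued after month 6 contribute only to the 180-day analysis; the sample-size plan does not rely on them.

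### With 30 pharmacies, GEE with the usual sandwich variance and a normal reference does not hold the 5% level; the excess is modest with arm only and grows as pharmacy-level covariates enter

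*Protocol article*

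**What the plan says.** All of this is in the Methods of the protocol article.

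- **Primary outcome (Statistical Methods).** Mean adherence is analysed by "generalized estimating equations (GEE) with an exchangeable correlation matrix and robust standard errors, with individuals as the analytical unit".
- **Secondary outcomes (Statistical Methods, text after Table 2).** The proportion with adherence of at least 80% and mean persistence are "analyzed using GEE with an exchangeable correlation matrix and robust standard errors".
- **Number of clusters (Sample Size).** The calculation arrives at 22 pharmacies. Enrolment is set higher, for a reason tied to the analysis: "30 will actually be enrolled as the planned statistical analysis requires a minimum of 15 clusters within each group". A reference is cited for that minimum.
- **Design figures (Sample Size).** "intracluster (or intraclass) correlation coefficient (ICC) of 0.0143", at least 25 subjects expected per pharmacy, and detection "with 80% power at a p < 0.05".
- **Covariates (Statistical Methods and Table 2).** Univariate and multivariable models are planned. Individual and pharmacy variables may enter if significant at P < 0.10 or clinically important. All first order interactions are tested. Table 2 offers five pharmacy-level variables. The text does not say which model supplies the primary test.

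The article is silent on the form of the robust variance, on any small-sample correction, and on the reference distribution.

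**The concern.** The sandwich variance is justified by a large number of clusters, not of patients. With about 30 clusters it is biased downward, because residuals are measured from means or fitted values that the same few clusters helped to estimate. A normal reference also ignores that the variance itself rests on roughly 28 degrees of freedom. Unequal cluster sizes make matters somewhat worse, and sizes will be unequal because Follow-up collects every new user at each pharmacy without a cap. Each pharmacy-level covariate uses up part of the 30 clusters.

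At stake is the false positive rate of the main comparison and the width of its interval, and the same for both secondary outcomes. Sample Size treats 15 pharmacies per arm as what the analysis needs. The question is whether that number alone delivers a 5% test.

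**Working it through.** **1. The plan's own figures.** The article gives no type I error figure beyond p < 0.05. Its cluster count follows from its stated 270 per group: 2 × 270 = 540, and 540 / 25 = 21.6, rounded up to 22. Enrolment is then raised to 30. Blocks of 6 give 30 / 6 = 5 full blocks, so 15 per arm. (Whether 270 follows from the stated SD is a separate matter and does not affect this check.)

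**2. Hand check, equal clusters, arm only.** Each pharmacy contributes 1/15 of its arm's mean, so the uncorrected sandwich variance has expectation (1 − 1/15) times the true value.
- Ratio of SE to truth: √(14/15) = 0.966.
- A nominal cut-off of 1.960 is then really 1.960 × 0.966 = 1.894 on a t scale with 30 − 2 = 28 df.
- P(|t28| > 1.894) = 6.9%, so the 95% interval covers about 93%.

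**3. Simulation under no effect, uncorrected sandwich, normal reference.** Inputs from the article: 30 clusters, 1:1 in blocks of 6, ICC 0.0143, mean size 25. Assumed: two-sided 5% test, normal outcome, cluster-size CV 0 or 0.5, some runs with mean size 75 or ICC 0.05, and the covariate distributions. There were 10,000 trials per scenario (Monte Carlo SE about 0.3 to 0.4 points).

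| Model | Scenario | Rejection at 5% | Mean SE / true SD |
|---|---|---|---|
| Arm only | size 25, CV 0 | 6.8% | 0.96 |
| Arm only | size 25, CV 0.5 | 7.6% | 0.94 |
| Arm only | size 75, CV 0.5 | 7.3% | 0.95 |
| Arm only | size 25, CV 0.5, ICC 0.05 | 7.4% | 0.94 |
| + 2 pharmacy parameters | size 25, CV 0 | 8.5% | 0.92 |
| + 4 | size 25, CV 0 | 9.7% | 0.87 |
| + 7 | size 25, CV 0 | 12.8% | 0.81 |
| + 7 | size 25, CV 0.5 | 15.4% | 0.76 |
| + 7 | size 75, CV 0.5 | 14.4% | 0.78 |
| Arm only, 120 clusters | CV 0.5 | 5.3% | 1.00 |

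The first row agrees with the hand check. The last row shows that the small number of clusters is the cause.

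Separately coded runs agree: 6.6 to 7.5% with arm only (CV 0 to 0.6), 8.6% with two parameters, and 14 to 16% with all seven. A binary outcome gave 7.5 to 7.7%. A skewed, bounded outcome gave 7.9% (4,000 trials, SE 0.4 points).

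**4. Where seven comes from.** Type has 3 levels (2 parameters), location 3 levels (2), volume 1, pharmacist coverage 1 and technician support 1: 2 + 2 + 1 + 1 + 1 = 7. That leaves 30 − 2 − 7 = 21 df.

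**5. Same data, corrected variance with a t reference on clusters minus cluster-level parameters.**

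| Model | Kauermann-Carroll + t | Mancl-DeRouen + t |
|---|---|---|
| Arm only | 4.8–5.6% | 4.1–4.8% |
| + 2 (CV 0) | 5.2% | 3.8% |
| + 4 (CV 0) | 5.2% | 3.4% |
| + 7 | 5.9–7.2% | 2.3–2.8% |

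The skewed outcome, arm only, gave 5.8% and 4.6%. With seven parameters one correction stays liberal and the other becomes conservative.

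**The case against.** The strongest reply is that nothing in the article says the standard errors are uncorrected or that a normal reference is used. A bias-corrected sandwich is also a robust standard error. This is a condensed article, and its analysis plan, which is not shown, is a normal place for such a detail. That stands, and it makes the point conditional. It does not remove the point, because the usual sandwich with a normal reference is a common reading of the words used, and the safeguard the article does state does not secure 5% under that reading.

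It is also fair that the authors considered cluster count and raised it from 22 to 30. The cited source for the minimum of 15 per group cannot be seen here and may itself presuppose a correction. So one can say only that 15 per arm is not sufficient on its own.

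A reader might infer more: that the plan commits to an invalid test, or that its false positive rate is about 16%. The documents do not support either. The arm-only excess is modest. The 13 to 16% range forces in all seven pharmacy parameters, whereas Table 2 lists variables available for selection, and the article's examples of clinically important ones (age and sex) are individual-level. Selection at P < 0.10 was not simulated, so the rate for the procedure as written is unknown.

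Persistence was not simulated. The same cause acts on it, but its size there is not shown.

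**Conclusion.** The point holds conditionally. If the robust standard error is the usual sandwich with a normal reference, the 30 pharmacies do not deliver a 5% test:

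- Arm only: about 6.5 to 7.7%, interval coverage about 92 to 93%.
- Two pharmacy-level parameters: about 8.5%.
- All seven: about 13 to 16%, as an upper case.

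The arm-only result does not depend on the assumed variation in cluster size, since equal clusters already give close to 7%. The larger figures depend on how many pharmacy-level covariates enter, which the article leaves to the data, and it names no primary model. Because 30 clusters perform well once the variance is corrected and adjustment is sparse, neither the GEE nor the number of pharmacies is at fault.

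**What to change.** Keep the GEE and the 30 pharmacies, and state the following before the data are released:

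1. For the primary and both secondary outcomes, use a small-sample corrected sandwich variance, for example Kauermann-Carroll, with a t reference on the number of clusters minus the number of cluster-level parameters.
2. Name the arm-only model, or one sparsely adjusted model, as the primary test.
3. Pre-specify a small number of pharmacy-level covariates in place of selection at P < 0.10. The correction alone is not enough with all seven.

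If the analysis plan already does this, a sentence confirming it is sufficient.

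**Cost.** A software option and a few sentences. Intervals widen by roughly 5 to 10% in the unadjusted model. With equal clusters the t reference contributes 2.048 / 1.960 = 1.045 and the variance correction √(15/14) = 1.035, together 1.045 × 1.035 = 1.08. The 8 pharmacies enrolled beyond the calculated 22 give some room for that loss. A further cost is that imbalance in pharmacy characteristics left out of the primary model can be examined only in secondary analyses.
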